### Data analysis

The raw data analysis will be performed using SPSS (v. 20.0) and will include descriptive, correlations, and repeated measures analysis of variance (ANOVA). Specifically, for the primary and second objectives, correlations will be run to examine the degree of relationship between the variables, and planned doubly multivariate repeated measures ANOVA’s will be performed to examine group differences between the intervention and control group. Descriptive statistics will be conducted for demographics, medical variables, adherence to the program, and physical activity behavior using means, standard deviations, and ranges as appropriate. As was previously mentioned, the statistician will be blinded to participant condition.

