### Sample size

Power calculations were derived using GPower 3.1 [19] The sample size/power calculation was based on relevant intervention literature [12,20,21] with natural killer cell activity as the primary outcome measure (Cohen’s d = .79). With an α of .05 and power of .80, a minimum sample size of 20 participants is required. To account for potential drop out, we will recruit an additional 20%, for a total of 24 participants.

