### Hematological and immunological recovery

#### Specimen collection

At baseline 2 Buccal Swabs will be collected to use for deoxyribonucleic acid (DNA) extraction. DNA specimens will be used to perform genotyping of activating and inhibitory KIR genes. The patient should not eat or drink anything for one hour prior to the specimens being taken. We will take one swab and rub the inside of right and left patient’s cheek for approximately 10 seconds. The swab will air dry for 1-2 minutes prior to replacing it into its container.

The baseline blood draw will be performed at the Unit 1 in the ACH (within 7 days prior to conditioning and transplant). The maximum blood volume to be drawn will be determined based on patient weight and other ordered blood work. A minimum of 7 mL will be required. The blood sample collection will be performed at baseline, day 7, 14, 30, 56, 85 and 180.

To avoid any acute EX effects, we will discourage any specific EX training 24 h before blood draws in the samples that will be collected at baseline and after transplant on day 14, 30, 56, 85 and 180. Research samples may be collected via central line or peripheral draw. For this study, we will store 1 aliquot each for peripheral blood mononuclear cells (PBMNCs) for every blood specimen serum. The aliquoted serum samples will be stored in our -86°C freezers and PBMNCs will be cryo-preserved at -150°C using liquid nitrogen based cell storage facility. All immune functional assays will be performed on cry preserved PBMNCs.

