#### Hematological and immune system assessment

Assessment of the impact of the EX intervention on the immune recovery of pediatric autologous SCT patients will be based on four parameters (a) Recovery of different leukocyte cell subset (e.g., T cells, NK cells, B cells, monocytes, neutrophils etc) in peripheral blood, (b) Expression of activating and inhibitory KIRs (c) Function of NK cells and their subsets and (d) Levels of different pro-inflammatory and regulatory cytokines in serum,

a) Recovery of NK cells and other immune cells subsets will be performed by flow cytometry enumeration of different blood leukocyte subsets including NK cells and its subsets (cytolysis and regulatory NK cells), T cells and its subsets (CD4, CD8, regulatory, naive and memory T cells), B cells, monocytes, neutrophils and dendritic cells.

b) Gene/allele carriage analysis for 8 inhibitory KIR genes (2DL1, 2DL2, 2DL3, 2DL4, 2DL5, 3DL1, 3DL2 and 3DL3); 6 activating KIR genes (3DS1, 2DS1, 2DS2, 2DS3, 2DS4 and 2DS5) and two pseudo genes (2DP1 and 3DP1) will be performed for all 24 patients. Gene expression analysis of 14 KIR genes will be done by RNA based real-time PCR analysis. Total RNA will be extracted from the PBMNCs for each time point and cDNA will be prepared using random primers and M-MLV reverse transcriptase enzyme. A quantitative real time PCR analysis will be performed to assess the expression of genes encoding for 8 inhibitory and 6 activating KIR genes. Quantitative PCR will be carried out with SYBR Green PCR method. The mRNA expression of different KIR genes will be normalized against GAPDH, and fold change in expression will be determined using ddCt method. Additionally, a flow-cytometry based protein expression analysis for 7 KIRs (4 activating and 3 inhibitory KIRs) on NK cells will also be performed. PBMNCs from each subject for each time point will be stained with fluorochrome labeled antibodies against different KIR molecules and markers specific for NK cells. Cells will be analyzed by multi-color flow cytometry. To quantify the amount of KIR expression on NK cells, we will determine the mean fluorescence intensity (MFI) for each KIR on NK cells.

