c) NK function will be assessed by measuring in vitro cytokine secretion and degranulation by different NK cell subsets (cytolysis and regulatory NK cells) on incubation with K-562 cell lines. PMNCs will be cultured with and without K562 cell in RPMI supplemented with 5% fetal bovine serum, glutamine (2 mM), Penicillin (100 U/ml) and Streptomycin (0.1 mg/ml) at 37°C in a humidified atmosphere containing 5% CO_2_. To measure degranulation, fluorochrome-conjugated antibody against human CD107a (a surrogate marker of degranulation) will be added to the cells at the start of culture as CD107a is only transiently expressed on T cell surface following activation-induced degranulation and it becomes internalized over time. Monessen will also added to the culture from beginning to ensure blockade of cytokine export from cells to the extra-cellular space and to provide neutral pH that maintains the fluorescence of FITC-conjugated CD107a antibody bound to CD107a, when internalized into the cell. At the end of the culture, cells will be stained with fluorochrome labeled antibodies against CD, CD3, CD56, CD16 and IFNγ and will be analyzed by multi-color flow cytometry. A cytolysis NK cell will be defined as CD3^neg^ CD56^dim^ CD16^pos^ NK cell while a regulatory NK cell will be defined as CD3^neg^ CD56^dim^ CD16^pos^ IFNγ^pos^ NK cell. Positivity for IFNγ and CD107a will correspond to the cytokine producing and degranulation functions respectively.

d) Assessment of cytokine levels in serum: A total of 30 cytokines including TNF-α, IFN-γ, IL-10, IL-6, IL-1α, IL-1β, IL-1R, IL-2, IL-12, TGF-β IL-15, and IL-17 etc will measured in the serum specimens for each time point using a bead-based array on Luminex.

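### Over seven blood draws in 20 to 24 children, the full group-by-time test of the planned doubly multivariate ANOVA fits none of the listed immune families, and it is not the single-outcome comparison that was powered

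*Protocol article*

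**What the plan says.** The Data analysis section names SPSS 20 and, for the primary and secondary objectives, says that "planned doubly multivariate repeated measures ANOVA’s will be performed to examine group differences between the intervention and control group". It does not say which outcomes share a model, which time points are the levels of the time factor, which of the resulting tests is read, or how baseline enters. It mentions no covariate adjustment, mixed model or imputation.

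On timing, Specimen collection says: "The blood sample collection will be performed at baseline, day 7, 14, 30, 56, 85 and 180". That is seven draws. Fitness, quality of life and related measures have four time points (Study design).

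The Hematological and immune system assessment section lists the immune outcomes: leukocyte subsets, KIR expression at transcript and protein level, NK function and serum cytokines. Two of the counts are explicit: "Gene expression analysis of 14 KIR genes will be done by RNA based real-time PCR analysis", and "A total of 30 cytokines including" a list of named examples.

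The Sample size section takes one outcome, NK-cell activity, with Cohen's d of .79, and concludes: "With an α of .05 and power of .80, a minimum sample size of 20 participants is required". It then adds: "we will recruit an additional 20%, for a total of 24 participants".

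**The concern.** A doubly multivariate repeated-measures ANOVA treats several outcomes at several times as one long response vector per child. Its full group-by-time test needs an error matrix of full rank, and the rank is capped by the number of children. Here the vectors are long and the children few, so the method named for the primary objective may not deliver its main test for the outcome sets that the protocol describes.

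Three further points follow from the choice of method:

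- A joint test of several outcomes is a different test from the single-outcome comparison on which the sample size rests.
- Repeated-measures GLM in SPSS works on complete cases, so one missing included draw removes a child from a trial that is already small.
- With no baseline adjustment mentioned, the baseline value may be spent as one more time level instead of being used to gain precision.

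**Working it through.** **Inputs.** N = 24 recruited and N = 20 required (Sample size); two groups of 12 (Study population); t = 7 draws (Specimen collection); t = 4 for the other assessments (Study design). Outcomes per family are from Hematological and immune system assessment. The count for NK function is an assumption: two functions (cytokine secretion, degranulation) in two NK subsets, so 4. Leukocyte subsets are counted as 11 (2 NK, 5 T, B cells, monocytes, neutrophils, dendritic cells), or 13 with total NK and total T cells.

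**The plan's own figure.** 24 is 20 × 1.2. The 20 itself is not reproduced by a two-sided two-sample t-test with d = .79, which needs 27 per arm. That is a separate matter and not evidence here; N = 20 and N = 24 are taken as given.

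**Rank condition.** For p outcomes at t times, the full group-by-time test works on p(t − 1) contrasts, and the error matrix has rank at most N − 2. So p(t − 1) ≤ N − 2 is needed.

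- 7 draws: 22/6 gives p ≤ 3 at N = 24; 18/6 gives p ≤ 3 at N = 20.
- 6 post-infusion draws only: 22/5 gives p ≤ 4; 18/5 gives p ≤ 3.
- 4 assessment times: 22/3 gives p ≤ 7; 18/3 gives p ≤ 6.

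| Immune family | p | p(t − 1), t = 7 | Complete cases needed, p(t − 1) + 2 |
|---|---|---|---|
| One outcome | 1 | 6 | 8 |
| NK function | 4 | 24 | 26 |
| KIR proteins | 7 | 42 | 44 |
| Leukocyte subsets | 11 | 66 | 68 |
| KIR transcripts | 14 | 84 | 86 |
| Cytokines | 30 | 180 | 182 |

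Building the error matrix numerically for p = 4, 7, 14 and 30 gave a rank of 22 (N = 24) or 18 (N = 20), below the dimension each time.

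**Degrees of freedom where it does fit.** The exact two-group F test has denominator df N − 1 − p(t − 1). At p = 3 and t = 7 this is 24 − 1 − 18 = 5, or 20 − 1 − 18 = 1 (critical F about 247 at the 5% level). At p = 1 it is 17 or 13.

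**Other tests from the same model.** The between-group multivariate test needs only p ≤ N − 2, that is 22 or 18; every family meets this except the 30 cytokines. The averaged test has error df (N − 2)(t − 1) = 132 or 108 and is computable for all families, if its sphericity-type assumption holds.

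**Missing draws (illustration only; the article gives no rate).** With independent missingness q per draw, expected complete cases are 24(1 − q)^7: 16.8 at q = .05 and 11.5 at q = .10. These leave room for at most 2 outcomes and 1 outcome.

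**Baseline.** If baseline is a level of the time factor, a constant post-baseline group effect enters the group main effect at 6/7 of its size (7 draws) or 3/4 (4 visits). The interaction is not diluted in this way.

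**What adjustment can give.** For a single visit, two-sided, d = .79 and 12 per arm, the noncentral t with effect d/√(1 − r²) gives power .46 at r = 0, .57 at r = .5 and .73 at r = .7. The correlations are assumed, and the comparator is an unadjusted t-test, not the planned ANOVA.

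**The case against.** The strongest reply is that the article never commits to putting a whole family into one model. It plans several ANOVAs, and the Sample size section names one outcome, which alone needs only 8 complete cases over seven draws. Sets of up to three outcomes also fit. The stated aim is group differences, for which the between-group test exists for every family but the cytokines, and the averaged test exists for all. All of this stands. A reader might infer that the primary analysis cannot be run at all; the article does not support that.

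The reply also holds on several further points:

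- Handling of missing draws is commonly left to an analysis plan that is not shown. Complete-case loss is a consequence of the named procedure, not something the article states. If missed draws cluster in the same children, fewer are lost than the illustration suggests.
- It is tempting to say that the early draws will yield too few cells, or that the complete cases would be the children who recover fastest. The article gives no data for either.
- Baseline as a time level is the natural reading, since baseline is listed among the repeated time points, but it is not stated.
- The trial is described as a source of preliminary and pilot data, which lowers the stakes.

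What the reply does not remove is the mismatch. The article fixes a method by name, and that method's full test fits no listed family over all seven draws. With one outcome the analysis is no longer doubly multivariate. The averaged test is not the one chosen, rests on an assumption that is hard to defend from day 7 to day 180, and still loses incomplete children.

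**Conclusion.** The point holds in limited form. Over all seven draws with 20 to 24 children, the full group-by-time multivariate test takes at most three outcomes, with 1 or 5 denominator degrees of freedom at three, and fits none of the immune families as listed. This rests on the arithmetic above; only the NK-function count of 4 depends on how the readouts are counted. The multivariate test also differs from the single NK-activity comparison used for the sample size.

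The loss of children with a missing draw follows from the procedure unless data are imputed; its size is unknown, and about 17 or 11 of 24 remaining is illustration only. The dilution by baseline is conditional on an unstated reading and affects the group main effect alone.

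This is a should-fix: a stated method for the primary objective is poorly matched to the data and can be replaced by a better one without new data, but a usable analysis can still be built from what is written.

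**What to change.** Rewrite the Data analysis paragraph so that the primary objective is tested on the one outcome that was powered, NK-cell activity, stating which assay readout that is. Use either of these:

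- a linear mixed model on post-baseline values, with baseline value, visit, group and group-by-visit as fixed effects; or
- ANCOVA at one pre-named visit, with the baseline value as covariate.

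Apply a small-sample degrees-of-freedom correction where the software offers it. Include every randomised child with post-baseline data, in the group assigned; ANCOVA can use only those with a value at the chosen visit, which favours the mixed model if draws are missed. Name the primary visit or contrast before unblinding.

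Fit the same model outcome by outcome to the other immune measures and label those results exploratory.

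The cost is one rewritten paragraph and giving up a joint multivariate test. No new data or visits are needed.

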### EX intervention 

This RCT will be a biphasic EX intervention.

Phase 1 – The inpatient phase will be performed at the ACH during conditioning and the isolated phase of autologous SCT.

Phase 2 – The outpatient phase will take place after discharge. The participants will participate in a 10 week mixed supervised and home-based EX program utilizing the Wii device.

In both phases participants will wear a portable heart rate monitor (RS300X Polar) when at the EX sessions to ensure safety and target the aerobic EX intensity between 50% and 70% of heart rate reserve (HRR), depending on the physical status of each child.

The training session will be cancelled if the child has platelet levels below 10.000/ μl, hemoglobin levels below 8 g/dl, fever greater than 38°C, pain, diarrhea, hemorrhage or any other complication(s) the oncologist thinks may worsen with EX. Additionally, a session may be cancelled if the child doesn’t want to participate.

#### Phase One: In-Patient Exercise Program

This program will consist of combined aerobic (20-30 minutes) and resistance training, designed on the basis of our previous experience with pediatric patients with cancer, and following the rules of the institutions for global benchmarks for strength training and aerobic EX in children and adolescents [7,14,22]. During the neutropenic phase, all training equipment (including cycle ergometers) will be sterilized before each training session, and the instructors will wear appropriate medical attire.

The strength EXs, will engage the major muscle groups (arm curl, elbow extension, bench press, leg extension, half squat, abdominals, supine bridge, and rowing), performing one set of 12–15 repetitions per EX.

#### Phase Two: Outpatient Exercise Program

Following the in-patient EX program, the participants of the intervention group will engage in a 10-week EX program consisting of 3 weekly sessions. The participants from Calgary will perform a combined supervised and unsupervised/home-based exercise program (2 unsupervised and 1 supervised sessions/week) with an average duration of 60 minutes/session. The participants from outside of Calgary will perform only the home-based EX program 3 days/week. The supervised and unsupervised EX plans will be individualized based on fitness assessment outcomes and current health status.

##### Supervised EX program

The supervised training session (Calgary-based participants) will be performed at the Thrive Centre at the University of Calgary 1 time/week and will be similar to the inpatient intervention.

##### Home-Based Exercise Program

Designed by exercise professionals and supervised by the parents, it will include 20-30 minutes of aerobic EXs and 30 minutes of strength and stretching EXs using Nintendo’s Wii console and Wii Fit/Wii Sports/Wii Dance games (from now on, named as Wii Fit/Sports/Dance).

Parents and children are going to be instructed on how to control the intensity of the EXs. Training adherence will be reported in a logbook, including reported training days and reasons for missed EX sessions. Training sessions will be declared valid if 80% of the planned session were performed. Participants will be reminded and encouraged to engage in their home-based workouts when they come to the Thrive Centre, and all participants (including those residing outside of Calgary) will receive a weekly phone call (from the research assistant) to encourage the participants to continue performing the EX program and answer any questions they or their parents may have.

### Measures

Once consent has been obtained, the research nurse will be responsible for instructing participants (parents and pediatric patient) (1) on the use of the accelerometers and log book, (2) on how to perform the food record, and (3) on the QOL assessment. The research coordinator will be responsible for contacting participants to perform the baseline HRF assessment. All baseline assessments will be performed before any conditioning regimen is administered. Additionally, the research coordinator will ensure all assessments are administered according to the protocol.

We will perform: (1) Hematological and Immunological Recovery, (2) Health and Lifestyle Assessment and (3) Health-Related Fitness Assessments (HRF).

### Hematological and immunological recovery

#### Specimen collection

At baseline 2 Buccal Swabs will be collected to use for deoxyribonucleic acid (DNA) extraction. DNA specimens will be used to perform genotyping of activating and inhibitory KIR genes. The patient should not eat or drink anything for one hour prior to the specimens being taken. We will take one swab and rub the inside of right and left patient’s cheek for approximately 10 seconds. The swab will air dry for 1-2 minutes prior to replacing it into its container.

The baseline blood draw will be performed at the Unit 1 in the ACH (within 7 days prior to conditioning and transplant). The maximum blood volume to be drawn will be determined based on patient weight and other ordered blood work. A minimum of 7 mL will be required. The blood sample collection will be performed at baseline, day 7, 14, 30, 56, 85 and 180.

To avoid any acute EX effects, we will discourage any specific EX training 24 h before blood draws in the samples that will be collected at baseline and after transplant on day 14, 30, 56, 85 and 180. Research samples may be collected via central line or peripheral draw. For this study, we will store 1 aliquot each for peripheral blood mononuclear cells (PBMNCs) for every blood specimen serum. The aliquoted serum samples will be stored in our -86°C freezers and PBMNCs will be cryo-preserved at -150°C using liquid nitrogen based cell storage facility. All immune functional assays will be performed on cry preserved PBMNCs.

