**Methods:**

This RCT has received approval from The Conjoint Health Research Ethics Board (CHREB) of the University of Calgary (Ethics ID # E-24476). Twenty-four participants treated for a malignancy with autologous stem cell transplant (5 to 18 years) in the Alberta Children’s Hospital will be randomly assigned to an exercise or control group. The exercise group will participate in a two-phase exercise intervention (in- and outpatient) from hospitalization until 10 weeks after discharge. The exercise program includes strength, flexibility and aerobic exercise. During the inpatient phase this program will be performed 5 times/week and will be supervised. The outpatient phase will combine a supervised session with two home-based exercise sessions with the use of the Wii device. The control group will follow the standard protocol without any specific exercise program. A range of outcomes, including quantitative and functional recovery of immune system, cytokine levels in serum, natural killer (NK) cells and their subset recovery and function, and gene expression of activating and inhibitory NK cell receptors, body composition, nutrition, quality of life, fatigue, health-related fitness assessment and physical activity levels will be examined, providing the most comprehensive assessment to date.

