**Figure 1 F1:**
[figure not shown]
Participants flow through SCORE study.

This study will examine the effect of two phases of an EX program on several health related outcomes in pediatric patients undergoing autologous SCT (Figure 2). The first phase of the EX program will be an inpatient intervention, beginning when the child is hospitalized undergoing conditioning therapy and continuing until discharge.

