**Figure 2 F2:**
[figure not shown]
SCORE study protocol.

The second phase will be a 10-week outpatient intervention, beginning once the child is discharged. We will utilize a mixed EX program, including supervised (at the University of Calgary) and home-based training incorporating the use of the Nintendo ® Wii device™ (Wii Fit, Wii Dance and Sports™ games).

Assessments include measures of QOL, fatigue, health-related fitness (HRF), physical activity levels and hematological and immunological reconstitution. Assessments will be completed at baseline, 30, 85 and 180 days post infusion day (day 0+). Hematological and immunological reconstitution will be assessed at the time points described above, plus at 7, 15 and 56 days post reinfusion. The baseline assessment will be completed within the two-month period prior to the conditioning regimen. The 30 day assessment is intended to capture the effect of Phase 1, the EX program during the hospitalization period (from conditioning regimen up to discharge). The 85 day assessment is intended to capture the early survivorship recovery period after an autologous SCT and the effect of Phase 2, EX program during the outpatient phase. The 180 day assessment will provide a mid-term follow-up of physical activity, QOL, fatigue and hematological and immunological reconstitution. These outcomes will allow us to examine the impact of an EX program implemented early during the SCT process 3 months after finishing the EX intervention on (i) physical activity levels (ii) QOL and fatigue iii) hematological and immunological recovery

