#### Control group

These subjects will not participate in any scheduled EX and will perform the same battery of tests as the intervention group. They will be offered an EX program upon completion of phase 2, to be held in the Thrive Centre, University of Calgary.

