1. Hematological and immunological reconstitution and exercise. The primary aim of this project is to examine the associations between EX, recovery of hematological and immunological reconstitution, and the relation with some disease outcomes in pediatric cancer patients undergoing autologous SCT (including duration of neutropenia, thrombocytopenia, anemia, fever, toxicity degree, chemotherapy completion rate infectious complications and event free survival) [41]. The clinical utility of autologous SCT is limited in part by treatment related toxicity [42]. Also, an absolute lymphocyte recovery of 500 cells/μl or more at day 15 after autologous SCT has been reported as a powerful and independent prognostic indicator of clinical outcomes. NK cells have antitumor activity, therefore an early NK cell engraftment with an early anti-tumor immune-surveillance might have a direct impact on survival post autologous SCT. Preliminary studies in children with cancer showed a decrease in NK lytic activity before and after cessation of cancer chemotherapy, especially in those with progressive disease [43,44]. Physical activity has the ability to promote an immune modulation that may involve multiple biological pathways, including a reduction in inflammation, an enhancement of anti-tumor response and may modulate killer cell immunoglobulin-like receptors (KIRs) [45]. Neither of the aforementioned mechanism has been studied in detail [46]. More research is needed to determine which inflammatory mediators and antitumor immune mechanism are more sensitive to EX.

2. Exercise, health-related fitness, quality of life and fatigue questionnaires. The specific objectives of this study are to examine the effect of an EX program on (a) QOL and fatigue outcomes across the SCT process and immediately after discharge, (b) to examine the associations between HRF indices, physical activity and QOL and fatigue outcomes.

Pediatric cancer patients undergoing SCT have an elevated risk for poor QOL and fatigue both during treatment and into survivorship, however this issue has to be studied in depth [4]. Some evidence suggests that EX may be a beneficial tool to improve fatigue and QOL in children with cancer [47]. New research suggest that fatigue is strongly associated with a diminish in physical activity levels [48], thus it is imperative to break the vicious cycle of fatigue in this population.

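### The 24-hour no-training rule before blood draws leaves out day 7, so that draw may mix acute exercise effects with immune recovery in the exercise arm only

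*Protocol article*

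**What the plan says.** Specimen collection in the protocol article gives the draw schedule: "The blood sample collection will be performed at baseline, day 7, 14, 30, 56, 85 and 180". The following paragraph names acute exercise as something to keep out of the samples: "To avoid any acute EX effects, we will discourage any specific EX training 24 h before blood draws". The same sentence then limits the rule to draws "in the samples that will be collected at baseline and after transplant on day 14, 30, 56, 85 and 180".

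On training, the Abstract (Methods) states: "During the inpatient phase this program will be performed 5 times/week and will be supervised". Study design describes the inpatient phase as "beginning when the child is hospitalized undergoing conditioning therapy and continuing until discharge". For the comparator, Control group states: "These subjects will not participate in any scheduled EX".

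Study design lists the immune assessments as the four main visits "plus at 7, 15 and 56 days post reinfusion". Its second early draw is thus one day later than the one under Specimen collection.

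**The concern.** The plan itself treats recent exercise as able to disturb blood measures, and it guards every draw but one. The unguarded draw sits in the most intensive part of the programme. The guarded list, by contrast, includes baseline, taken before any trial training, and day 180, after the exercise arm has finished.

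Any disturbance would be tied to the assigned arm. Randomisation does not balance it and blinded assessment does not remove it, because a session shortly before sampling is part of being in the exercise arm. The primary objective asks whether exercise changes immune recovery. A day-7 difference between arms could then reflect a passing response to the last session, a change in recovery, or both, and the data would not tell these apart. Once the samples are taken, this cannot be repaired.

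**Working it through.** No figure in the plan needs reproducing here. The check compares lists and then gives a simple estimate of exposure.

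**1. Draws against rule (both from Specimen collection).**
- Draws: baseline, 7, 14, 30, 56, 85, 180 (seven).
- Covered by the 24-hour rule: baseline, 14, 30, 56, 85, 180 (six).
- Difference: day 7 only.

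**2. Who is training at day 7.** The inpatient programme runs from conditioning to discharge, so it includes day 7 for any child still in hospital. The inpatient programme section provides for sterilising equipment before each session during neutropenia, so training in this period is intended. Controls have no scheduled exercise.

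**3. Share of day-7 draws within 24 hours of a session.** Inputs: 5 sessions per 7 days (Abstract); 12 children in the exercise arm (Study population); cancellation rate *c*, which the document does not give and which is assumed here. Also assumed: the child is still an inpatient, and the draw is unrelated to the session calendar.

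Formula: share = (5/7) × (1 − *c*).

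| Assumed *c* | Share, exercise arm | Children out of 12 | Controls |
|---|---|---|---|
| 0 | 5/7 = 0.714 (71%) | 12 × 0.714 = 8.6 | 0% |
| 25% | 0.714 × 0.75 = 0.536 (54%) | 12 × 0.536 = 6.4 | 0% |
| 50% | 0.714 × 0.50 = 0.357 (36%) | 12 × 0.357 = 4.3 | 0% |

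The control figure refers to scheduled sessions. The table measures exposure, not bias: the document gives neither size nor sign for the acute effect.

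**4. Whether day 7 is used.** Hematological and immune system assessment has KIR gene expression and serum cytokines measured at every time point. Data analysis plans repeated-measures ANOVA for the primary objective without listing the time points, so day 7 is neither named nor set aside.

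**5. The second early draw.** Study design gives day 15. Specimen collection gives day 14 twice, in the schedule and in the 24-hour sentence. This mismatch is independent of steps 1 to 4.

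**The case against.** The best defence is that little training may take place just before day 7. All participants receive myeloablative conditioning. Under EX intervention, sessions are cancelled for low platelets or hemoglobin, fever, pain, diarrhea, hemorrhage or other complications, and may be cancelled if the child declines. This stands as a limit on size: 71% is a ceiling, and the true share is unknown. It does not explain the omission, since the same cancellation rules apply at the draws that are covered.

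A second defence is that day 7 is one of six post-infusion draws, and that Study design assigns the effect of the inpatient phase to day 30 and that of the outpatient phase to day 85, both covered. This also stands in part. It limits the reach of the problem, but nothing in the document keeps day 7 out of the group comparison.

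Three stronger readings are tempting, and the document does not support them:
- *Day 7 will make recovery look faster in the exercise arm.* The document speaks of acute effects without direction, size or duration.
- *The primary result is compromised.* The time points entering the ANOVA are not stated, and the statistical analysis plan is not shown.
- *A day-14 sample defeats the plan's own benchmark.* The Discussion says that a lymphocyte level "at day 15 after autologous SCT has been reported as a powerful and independent prognostic indicator of clinical outcomes". That is background, not a defined endpoint or a planned analysis. The day-14/day-15 difference is a one-day mismatch to be reconciled, no more.

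**Conclusion.** The omission is certain: day 7 is the only scheduled draw outside the 24-hour rule, and no reason is given. It may be an oversight or deliberate. Followed as written, the plan leaves one immune time point open to an arm-specific disturbance that it sets out to avoid elsewhere.

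How far this distorts the comparison is unknown. Exposure could reach 71% of exercise-arm draws, or about 54% or 36% under the assumed cancellation rates, against none in controls. These figures hold only if draws are unrelated to the session calendar and children are still in hospital at day 7. The supported conclusion is that the draw may mix the two effects, not that it does. The point is worth correcting because the change is small and cannot be made after sampling.

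**What to change.** - Add day 7 to the list in the 24-hour sentence under Specimen collection, and schedule that draw after a non-training day; five sessions a week leave two. If the omission is deliberate, give the reason.
- Record hours since the last session at every draw. The rule only discourages training, so breaches are possible at the other draws too.
- Add a sensitivity analysis of the group comparison with day 7 left out for both arms.
- Do not exclude individual day-7 values because they were drawn too soon after a session. Only exercise-arm values could be lost, and they would come from children well enough to train. In a complete-case repeated-measures ANOVA, each such value could remove a whole child from an arm of 12.
- Separately, reconcile day 15 (Study design) with day 14 (Specimen collection) for the second early draw.

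Cost: an edited sentence, a scheduling note, one recorded field and one extra analysis. The day-7 draw or one session may shift by a day. The time-since-session field would reveal the arm, so it should be held apart from the blinded assessors and the blinded analysis file until the main comparison is done.
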